## Abstract

**Simple Summary:**

Surgical treatment of pelvic sarcoma involving the bone is the standard of care but is associated with several treatment sequelae and reduced functional quality of life. Treatment with photon and proton radiotherapy is associated with relapse. Carbon ion radiotherapy may reduce both relapse rates and treatment sequelae. The PROSPER study is a tricontinental, nonrandomized, prospective, three-arm, pragmatic trial evaluating carbon ion radiotherapy, proton therapy, and the surgical treatment of pelvic sarcoma involving the bone. We describe the rationale and design of this clinical trial currently open to enrollment.

**Abstract:**

Surgical treatment of pelvic sarcoma involving the bone is the standard of care but is associated with several sequelae and reduced functional quality of life (QOL). Treatment with photon and proton radiotherapy is associated with relapse. Carbon ion radiotherapy (CIRT) may reduce both relapse rates and treatment sequelae. The PROSPER study is a tricontinental, nonrandomized, prospective, three-arm, pragmatic trial evaluating treatments of pelvic sarcoma involving the bone. Patients aged at least 15 years are eligible for inclusion. Participants must have an Eastern Cooperative Oncology Group Performance Status score of two or less, newly diagnosed disease, and histopathologic confirmation of pelvic chordoma, chondrosarcoma, osteosarcoma, Ewing sarcoma with bone involvement, rhabdomyosarcoma (RMS) with bone involvement, or non-RMS soft tissue sarcoma with bone involvement. Treatment arms include (1) CIRT (*n* = 30) delivered in Europe and Asia, (2) surgical treatment with or without adjuvant radiotherapy (*n* = 30), and (3) proton therapy (*n* = 30). Arms two and three will be conducted at Mayo Clinic campuses in Arizona, Florida, and Minnesota. The primary end point is to compare the 1-year change in functional QOL between CIRT and surgical treatment. Additional comparisons among the three arms will be made between treatment sequelae, local control, and other QOL measures.

## 1. Introduction

An estimated 3910 cases of bone cancer are diagnosed annually in the US, constituting 0.2% of all newly diagnosed cancer cases [1]. These neoplasms include chordoma, chondrosarcoma, Ewing sarcoma, and osteosarcomas, among others. Up to 14% of all malignant bone tumors are located in the pelvic bones [2]. Multimodal treatment is always required and should be performed at a center with expertise in treating sarcoma [3]. Local treatment may include surgery, radiotherapy, or both, depending on the tumor location, histopathologic characteristics, anticipated surgical resection issues, anticipated surgical sequelae, and patient preferences. 

Many oncologists consider surgical treatment to be the optimal choice for the local treatment of pelvic bone sarcoma because surgical treatment yields higher local control rates than does definitive radiotherapy [4,5,6,7]. For example, Houdek et al [5] reported a 5-year local control rate of 80% with surgical resection for sacrococcygeal chordoma, as compared with a 70% to 75% local control rate with definitive radiotherapy. Similarly, the Children’s Oncology Group reported a six-fold higher local recurrence rate for pelvic Ewing sarcoma treated with definitive radiotherapy than with surgical treatment alone [8]. Additionally, the Cooperative Osteosarcoma Study Group reported that the omission of surgical treatment was correlated with a high risk of relapse among a cohort of patients with pelvic osteosarcoma [9]. Despite these findings, each form of local therapy poses substantial challenges with regard to disease outcomes, as well as late adverse events, reduced quality of life (QOL), and poor functional outcomes.

For resectable pelvic bone and soft tissue sarcoma, surgical treatment may require extensive resection and reconstruction. Surgical treatment sequelae are more likely to occur when the tumor involves multiple pelvic bones, the lumbosacral plexus, and/or the pelvic vasculature [10]. Additionally, the preservation of lower extremity, bowel, and bladder function often requires accepting close surgical margins. Therefore, surgical treatment may negatively affect patient QOL and function [11,12]. 

Definitive radiotherapy is used as an alternative to surgical treatment for pelvic bone sarcoma when resection is not feasible or would result in severe treatment sequelae and/or when the patient is not a candidate or is unwilling to undergo surgical treatment [4]. However, high radiotherapy doses are needed for local control in this setting because of the low α/β ratio for most of these bone tumors [13]. National Comprehensive Cancer Network (NCCN) guidelines recommend doses greater than 70 Gy for bone sarcoma, which exceeds the tolerance of surrounding healthy pelvic tissues, such as the small bowel and lumbosacral plexus. For this reason, the NCCN recommends the use of proton beam therapy (PT) or carbon ion radiotherapy (CIRT) for treating pelvic bone sarcoma [4]. 

With conventional photon radiotherapy, the maximum radiation dose is deposited after entering the body and is attenuated as it passes through the entire body. This dose distribution limits the use of the most effective radiotherapy doses and exposes a considerable amount of healthy tissue to the harmful effects of radiotherapy. PT uses positively charged proton ions and delivers a maximum dose to a specific depth without an exit dose because of the physical characteristics of the Bragg peak. Accordingly, PT delivers a high radiotherapy dose to the treatment volume while exposing healthy tissues beyond the target volume to a lower dose than does conventional photon radiotherapy. This PT dose distribution also permits a safer dose escalation and/or hypofractionation. Many studies have reported that PT is safe and effective for the treatment of pelvic sarcoma [14,15,16,17]. 

CIRT uses charged carbon ions that are heavier than proton ions. CIRT also has the physical advantage of the characteristic Bragg peak, which allows for the depth of the carbon ion beam to be modulated and protection of healthy tissues around the treatment volume. Moreover, carbon ions have high linear energy transfer (LET) and a low oxygen enhancement ratio, with high relative biological effectiveness (RBE) that results in clustered DNA damage that is difficult to repair and that causes extensive tumor cell death [18,19]. In addition, CIRT can effectively enhance apoptosis in radioresistant cancer stem cells, which have been characterized in bone sarcomas. These radiobiological characteristics of CIRT appear to improve local control outcomes of radioresistant pelvic bone sarcomas such as chordoma, osteosarcoma, and chondrosarcoma [20,21,22,23,24,25,26]. 

Currently, only a few international institutions use CIRT to treat pelvic bone sarcoma [27]. Accordingly, data evaluating the potential differences in oncologic outcomes, treatment sequelae, and functional outcomes between CIRT and surgical treatment or PT are scarce. Recently, Yolcu et al [28] compared outcome data from registries of patients with sacral chordoma treated with the following: (1) CIRT at the National Institute for Quantum and Radiological Science and Technology (QST Hospital) in Chiba, Japan; (2) en bloc surgical resection at Mayo Clinic in Rochester, MN, USA; (3) en bloc surgical resection with or without photon therapy at various institutions reporting to the National Cancer Database (NCDB). Overall survival rates were worse with photon therapy, as reported by the NCDB, than with CIRT at QST Hospital. Additionally, the overall survival rate was similar for patients treated with CIRT and those treated with surgical resection (with or without radiotherapy), as reported by the NCDB. When comparing the outcomes of patients treated at QST Hospital with those treated with en bloc surgical resection at Mayo Clinic, no significant difference in local control or overall survival was observed. However, patients who underwent CIRT had less peripheral motor neuropathy and marginally better functional outcomes. Similar outcomes were reported by Outani et al [12]. 

Both of these studies were limited by a retrospective analysis of different combinations of patient registry data, with only physician-reported outcomes. The SACRO trial (NCT02986516), an international, multicenter, observational study of localized sacral chordoma, includes both randomized arms of surgical treatment vs. high-dose definitive radiotherapy (CIRT, PT, and mixed photon-PT), as well as two nonrandomized prospective arms. In the nonrandomized arms, surgery or PT is selected according to patient and physician preference. This trial is ongoing, and accrual has occurred as planned for the nonrandomized arms but has been difficult for the randomized arms. For this reason, we developed the PROSPER study (NCT05033288). This trial is a pragmatic, prospective, multicenter study comparing functional outcomes, treatment sequelae (reported by both patients and physicians), and local control for patients with pelvic bone sarcoma who undergo surgical treatment, PT, or CIRT.

## 2. Research Methods and Analysis

The purpose of the PROSPER study (ClinicalTrials.gov, NCT05033288) was to compare patient-reported outcomes, adverse events/treatment sequelae, and local tumor control for bone/soft tissue sarcoma involving the pelvic bone, among three treatment arms: (1) CIRT, (2) surgical treatment, and (3) PT (Figure 1). 

The primary aim of the study is to compare patient-reported health-related QOL outcomes and treatment sequelae after CIRT with those after surgical treatment. We acknowledge that the CIRT and surgical treatment arms will have considerably different disease-specific characteristics (e.g., tumor stage, size, and extent), with a disproportionate number of patients who undergo CIRT having larger and higher-stage tumors involving the sacral plexus. However, if the functional outcomes and treatment sequelae data show an advantage for CIRT, despite these differences, then CIRT would most likely yield the same, or even better, favorable functional outcomes when comparing the two treatment arms containing disease severity-matched patient cohorts.

The secondary aim of the study is to determine whether CIRT improves local control in comparison with PT. This aim was chosen because CIRT is considered to be more biologically effective than radiotherapies with a lower LET (i.e., photon therapy or PT) for treating radioresistant tumors and may reduce the risk of local recurrence. 

The PROSPER study was designed as a prospective, parallel cohort study. Although a randomized study would provide a higher level of evidence, several feasibility and administrative challenges would arise with a randomized trial. Specifically, randomization between the surgical treatment and definitive treatment with the CIRT or PT arms would have been problematic. Even the ongoing SACRO trial, which has enrolled more than 100 patients, could not randomly assign patients, and all patients were treated in the prospective cohorts. 

In the PROSPER study, patients with unresectable tumors will be enrolled in the trial, although they will not be eligible to be randomly assigned to the surgical treatment arm. Although randomization between the CIRT and PT treatment arms would potentially be possible, the logistics of randomizing these arms would still pose challenges. The PROSPER study protocol was activated at all 3 Mayo sites in 2022: at Mayo Clinic in Florida on 20 January, Mayo Clinic in Arizona on 14 February, and Mayo Clinic in Minnesota on 1 June. The participating CIRT sites are currently preparing to activate the trial. To date, no patients have been enrolled in the PROSPER study. We anticipate that the enrollment period will require up to 36 months for accrual. 

Mayo Clinic will enroll most of the patients in the trial but will not have the ability to treat patients with CIRT until 2027, when Mayo Clinic in Florida will open its CIRT center to patients. Although Mayo Clinic investigators could send patients to Europe or Asia to receive CIRT, treatment costs and travel restrictions would be challenging because the reimbursement of costs associated with sending patients abroad is currently unresolved for CIRT. Indeed, during the development of the PROSPER study, a randomized trial led by the University of Texas Southwestern Medical Center assessing CIRT vs. intensity-modulated radiotherapy/PT treatment of patients with pancreatic cancer (NCT03536182) was opened, closed, and withdrawn when the COVID-19 pandemic restricted travel, as well as the ability to randomly assign US patients to centers with CIRT in Europe and Asia.

Because of the low incidence of bone/soft tissue sarcoma involving the pelvis, the PROSPER study was designed to be pragmatic, with generous eligibility criteria to avoid ineligibility (except for critical factors) and encourage collaboration among several CIRT centers. The CIRT centers participating in the PROSPER study use different RBE dose calculation models, dose fractionation schemes, and target volumes. We concluded that allowing these variations in the study was important to engage various international CIRT centers in one of the first multicontinental CIRT studies [29]. Although permitting such CIRT variability in our study will yield a heterogeneous cohort in the CIRT treatment arm that could obscure significant outcomes, we will scrutinize the results according to each treatment plan, which will be centralized, and evaluate the patterns associated with different functional outcomes, adverse events/treatment sequelae, and rates of local recurrence.

Inclusion criteria for enrollment in the PROSPER study are as follows: male and female patients aged at least 15 years, with an Eastern Cooperative Oncology Group Performance Status score of 2 or less, newly diagnosed disease, and histopathologic confirmation of pelvic chordoma, chondrosarcoma, osteosarcoma, Ewing sarcoma with bone involvement, rhabdomyosarcoma with bone involvement, or nonrhabdomyosarcoma soft tissue sarcoma with bone involvement. Patients will be required to provide written informed consent and complete questionnaires by themselves, or with assistance, and must agree to use adequate contraception if of childbearing age. Patients will be excluded if they have distant metastatic disease, as evidenced by clinical examination or imaging, or if they are receiving palliative-intent treatment, have recurrent disease, or have received prior radiotherapy to the tumor site or the surrounding area that would cause an overlap of radiotherapy doses in healthy tissues.

CIRT facilities in Europe and Asia will enroll patients eligible for treatment with curative-intent CIRT in treatment arm 1. Mayo Clinic campuses in Arizona, Florida, and Minnesota will enroll patients in treatment arm 2 if they are examined in the Mayo Clinic orthopedic oncology or neurosurgery departments and deemed by a multidisciplinary team to be eligible to undergo definitive surgical treatment. Mayo Clinic (all campuses) will enroll patients in treatment arm 3 if they are examined in the Mayo Clinic radiation oncology department and deemed by a multidisciplinary team to be eligible to receive definitive treatment with PT.

### 2.1. Treatment Arm 1

Five CIRT centers participated in the development of the PROSPER study, including QST Hospital (Chiba, Japan), Shanghai Proton and Heavy Ion Center (Shanghai, China), Italian National Center for Oncological Hadrontherapy (Pavia, Italy), MedAustron (Wiener Neustadt, Austria), and the Heidelberg Ion Beam Therapy Center (Heidelberg, Germany). For all sites, CIRT is a standard-of-care treatment for unresectable sarcoma tumors involving the bone(s) of the pelvis. In accordance with the pragmatic approach of the PROSPER study, no strict guidelines were developed to specify target delineation, treatment planning, RBE dose calculation model, total dose, or dose fractionation. Each site has developed its own method for managing these tumors, which was a requirement for multicenter collaboration. However, Digital Imaging and Communications in Medicine (DICOM)-standardized treatment plans will be centralized for review, including variations in target selection and delineation, target coverage, organ at-risk (OAR) dose constraints, total dose, and dose fractionation. Adjuvant systemic chemotherapy is allowed according to institutional policies. 

### 2.2. Treatment Arm 2

Surgical treatment will be performed at all 3 Mayo Clinic campuses (Phoenix, AZ, USA; Jacksonville, FL, USA; Rochester, MN, USA). The specific type of surgical procedure will be at the discretion of the surgeon for each patient. Adjuvant radiotherapy and/or chemotherapy will be allowed according to institutional approaches to treatment. 

### 2.3. Treatment Arm 3

PT will be administered at all 3 Mayo Clinic campuses. Target delineation, treatment planning, total dose, OAR dose constraints, and dose fractionation will be determined by the treating radiation oncologist, but physicians are expected to use previously agreed-upon health system treatment approaches.

### 2.4. Outcomes Measures

All patients will complete Patient-Reported Outcomes Measurement Information System-29 (PROMIS-29) and European Organisation for Research and Treatment of Cancer (EORTC) colorectal cancer–specific quality of life (QLQ-CR29) questionnaires at baseline and posttreatment time points.

Baseline patient-, disease-, and treatment-specific details will be collected and entered into our Research Electronic Data Capture (REDCap) system. After treatment is completed, the full radiation data set, including initial and any adaptive modifications to the data set (DICOM RT_PLAN, RT_STRUCT, RT_IMAGE, RT_DOSE), will be anonymized (except for the patient study number) and transferred to the Mayo Clinic DICOM database. Dose–volume histograms (DVHs) will be provided for the following OARs: the small bowel, large bowel, cauda equina, sacral plexus [30], femoral heads, rectum, and bladder. Oncologic outcomes and adverse events will also be entered in our REDCap system.

### 2.5. Follow-Up

Standard follow-up will include medical history and physical examination with Eastern Cooperative Oncology Group Performance Status scores at approximately 3, 6, 12, 24, 36, 48, and 60 months. Magnetic resonance imaging of the pelvis will be preferred, but computed tomography or positron emission tomography/computed tomography will be acceptable if the patient is unable to undergo magnetic resonance imaging. Imaging findings, treatment sequelae, and PROMIS-29 and EORTC QLQ-CR29 responses will be collected at each follow-up examination.

Assessments of treatment sequelae will include the following Common Terminology Criteria for Adverse Events v5.0: gastrointestinal tract (diarrhea, nausea, vomiting, perforation, stenosis, ulcer, colitis, obstruction, fistula, fecal incontinence, and necrosis), urinary tract (dysuria, fistula, incontinence, urgency, and retention), musculoskeletal (osteonecrosis, soft tissue necrosis, fracture, muscle weakness, lower limb, extremity pain, pelvic pain, lymphedema, soft tissue fibrosis, and gait disturbance), sexual function (dyspareunia in women and erectile dysfunction in men), and nervous system (motor neuropathy, sensory neuropathy, phantom pain, and radiculitis) disorders.

### 2.6. Statistical Consideration

For our primary aim of comparing patient-reported QOL outcomes and treatment sequelae after CIRT with those after surgical treatment, we will use the functional domain of the PROMIS-29 questionnaire. We will specifically compare the mean difference in the functional QOL from before treatment (baseline) to 1 year after the end of treatment, between treatment arms 1 and 2, with a one-sided, two-sample *t* test of independent means. On the basis of previous studies and retrospective clinical data, we conservatively expect a mean decrease in functional QOL of 2 points for treatment arm 1 and 4.6 points for treatment arm 2 (higher than the defined minimal clinically important difference), with an SD of 4 points in both arms. We will obtain 80% power (α = 0.05) to detect significantly improved functional QOL between the 2 treatment arms with 30 patients in each arm (*N* = 90 patients for all 3 arms).

To reduce the likelihood of underpowering the trial because of screening failures, loss to follow-up, death, and other causes that could lower the number of patients reaching the 5-year follow-up study end point, we will recruit an additional 6 patients per treatment arm (*n* = 36 patients per arm, *N* = 108).

Data will be stored and maintained in the external Mayo Clinic REDCap system. Analyses for the primary aim will be completed when all eligible patients have completed the PROMIS-29 questionnaire at baseline and 1 year after the end of treatment. The PROMIS-29 functional score will be calculated, and median, mean, and 95% CI values will be compared between each treatment arm, with one-sided, two-sample *t* tests. Analyses for the secondary aim of determining whether CIRT improves local control in comparison with PT will be completed after the last treated patient has been followed for 3 years. Analysis will be completed for all patients; however, because of the possibility of heterogeneous outcomes resulting from differences in histopathologic findings, analyses of local control will be stratified according to histopathologic characteristics. Subset analyses will also be performed for sacral chordoma vs. non-sacral chordoma. The proportion of patients with local control at 3 years and 95% CI in treatment arms 1 and 3 will be calculated with a one-sided noninferiority test. 

The Kaplan–Meier method with likelihood ratio tests will be used to evaluate all clinical outcomes, which will include local recurrence, regional progression, distant metastases, progression-free survival, and overall survival, for each treatment arm. Subset and stratified analyses according to histopathologic characteristics will also be conducted for all time-to-event analyses. 

Exploratory analyses of local control between arm 2 and arms 1 and 3, treatment sequelae, and DVH data will be performed with standard logistic regression analysis of acute- (<6 months) and late-onset (≥6 months) treatment sequelae. Area under the receiver operating characteristic curve analyses will be performed for each DVH measure to determine the effect of the treatment modality on treatment sequelae, QOL, local control, and survival.

The participating CIRT centers will have considerable heterogeneity regarding patient selection, treatment prescription, total dose per fraction, target and OAR contouring, OAR constraints, and use of RBE dose calculation models. Therefore, CIRT data will be analyzed separately for each institution. In the unlikely event of marked differences in outcomes among these centers, sub-analyses will be performed, and we will consider publishing data for each (deidentified) institution separately.

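### The primary-analysis trigger cannot be met, read literally, once any patient dies or misses the 1-year form, and the stated t test on change can use only patients with both scores

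*Protocol article*

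**What the plan says.** All of this is in the protocol article, mostly in section 2.6 (Statistical Consideration).

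- **Trigger.** "Analyses for the primary aim will be completed when all eligible patients have completed the PROMIS-29 questionnaire at baseline and 1 year after" treatment ends. The secondary analysis of local control has a different kind of trigger, set by time: three years of follow-up for the last patient treated.
- **Primary test.** The plan will "compare the mean difference in the functional QOL from before treatment (baseline) to 1 year after the end of treatment, between treatment arms 1 and" arm 2 (surgery). It does so "with a one-sided, two-sample" t test.
- **Sample size.** It assumes "a mean decrease in functional QOL of 2 points for treatment arm 1 and 4.6 points for treatment arm 2" and, for the spread, "with an SD of 4 points in both arms", and gives 30 per arm for 80% power.
- **Allowance.** Six more patients per arm (36 in place of 30) are recruited against "screening failures, loss to follow-up, death, and other causes that could lower the number of patients reaching the 5-year follow-up study end point".
- **Data available.** Section 2.5 (Follow-Up) schedules visits at about 3, 6 and 12 months and then yearly to 60 months, and "PROMIS-29 and EORTC QLQ-CR29 responses will be collected at each follow-up examination".

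**The concern.** Two stated features do not sit well together. The trigger asks for complete 1-year questionnaires from all eligible patients. The paragraph before it budgets for patients who will not supply one. If the trigger is taken as written, the primary analysis waits for an event that the plan itself does not expect. If it is relaxed informally, its timing becomes a matter of judgement in an open-label, non-randomized study.

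The test raises a separate issue. A t test on change needs both scores, so a patient without a 1-year score contributes nothing, even when 3- and 6-month scores exist. Patients who relapse, deteriorate or die are the likely non-completers. Section 2 expects arm 1 to hold disproportionately more large, high-stage tumours, and the Discussion acknowledges differences in health care access and baseline characteristics for arm 1. Unequal loss related to outcome is therefore plausible. It would favour whichever arm loses more of its poorly functioning patients.

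**Working it through.** **1. The plan's own figure.** Inputs from section 2.6: difference 4.6 − 2.0 = 2.6 points, SD 4, one-sided α = 0.05, power 80%.

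n per arm = 2 × SD² × (z₀.₉₅ + z₀.₈₀)² / difference² = 2 × 16 × (1.645 + 0.842)² / 2.6² ≈ 29.3, rounded up to 30.

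Power at 30 per arm is 80.9% by the normal approximation and 80.0% by the noncentral t. The stated 30 reproduces. Inflating for loss, 30 / (1 − 1/6) = 36 also reproduces, and the implied loss is 6/36 = 16.7%.

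**2. Chance that the literal trigger is met.** With independent losses, P(all complete) = (1 − loss)^72 for the 2 × 36 = 72 patients in arms 1 and 2.

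| Loss per patient | Source | P(all 72 complete) |
|---|---|---|
| 2% | assumed | 23% |
| 5% | assumed | 2.5% |
| 10% | assumed | 0.05% |
| 16.7% | implied by 6/36 | about 0.0002% |

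If the sentence covers all three arms (108 patients), the chances are lower still: 11%, 0.4%, 0.001% and about 3 × 10⁻⁹.

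**3. What loss does to power.** At 16.7% loss, 30 per arm remain and power is 80.0%. At an assumed 25% loss, 27 per arm remain and power is 76.2%. At the planned loss the risk is therefore bias, not lack of patients.

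**4. What loss could do to the contrast.** Simulation inputs: no true difference, SD 4 and 36 per arm. A worse own change makes a missing 1-year score more likely (logistic slope 1 per SD). The slope and the unequal loss rates are assumptions.

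| Loss, arm 1 vs arm 2 | Spurious advantage for arm 1 | One-sided type I error |
|---|---|---|
| 16.7% vs 16.7% | about 0 | about 5% |
| 25% vs 10% | about 0.5 points | about 12% |
| 30% vs 5% | about 0.8 points | about 20% |

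Against the planned 2.6 points, 0.5 is about a fifth (0.5 / 2.6 = 19%). If arm 2 lost more, the bias would run the other way.

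**5. What earlier scores can recover.** If missingness depends on the observed 6-month score, a model using the 3- and 6-month data cut the bias from 0.47 to 0.03 points. If it depends on the unobserved 1-year change, adjusting for two earlier scores (assumed inter-visit correlation 0.4 to 0.8) cut a bias of about 0.5 only to between 0.40 and 0.15.

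**6. Time point of the allowance.** The powered comparison is at 1 year and the local-control analysis at 3 years. No powered comparison is described at 5 years. Keeping 30 of 36 to year 5 would need annual retention of (30/36)^(1/5) = 0.964, a loss of at most 3.6% a year. The same 16.7% therefore means something quite different at 1 year and at 5.

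**The case against.** The strongest reply is that the trigger sentence is loose drafting. It sets timing, not an analysis set, and a team that recruits 36 to keep 30 clearly does not expect complete data. If eligible means still alive and in follow-up, the trigger works and the probabilities in step 2 do not apply. That is fair as to intent. But the reading is not stated, and it would make the primary comparison conditional on survival and completion. Either way the sentence needs repair.

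A reader might infer that the plan declares a completers-only analysis set. It does not. The restriction follows from the named test, and a full protocol or analysis plan, not shown here, could add rules for missing scores and deaths. Their absence from an article is no finding. The point rests on the method that the article does state.

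A reader might also infer that the 3- and 6-month scores go unused. The article says only that the primary test takes baseline and 1 year; other quality-of-life comparisons are planned.

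The bias figures depend on unequal loss rates that appear nowhere in the documents. The plan's own allowance is equal across arms, and equal 16.7% loss under this mechanism gives essentially no bias. That objection stands, and it limits the claim to a vulnerability. It also stands that a repeated-measures model does not remove bias when missingness depends on the unobserved score, and that it implicitly carries scores beyond death.

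**Conclusion.** The concern holds in a limited form. The trigger, as worded, conflicts with the losses that the same section plans for. This needs no assumption beyond a literal reading; only the probabilities assume independent losses and, apart from 16.7%, chosen loss rates.

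The primary test can use only patients with both scores and so is open to bias under differential, outcome-related loss. That is plausible here, but its size is unknown. The illustrations run from essentially zero (equal 16.7%) to about 0.5 points and 12% type I error (25% versus 10%), or about 0.8 points and 20% (30% versus 5%). They do not show that the primary result will be biased.

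Tying the allowance to 5 years does not fit a comparison powered at 1 year. It might be read as a sample-size error, but 30 and 36 per arm both reproduce. The change should be made, at modest priority, before the primary data are analysed.

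**What to change.** 1. **Trigger.** Run the primary analysis when the last treated patient has passed the 1-year assessment window, died or withdrawn. This matches the time-based form already used for the secondary aim.
2. **Estimator.** Take the 1-year contrast between arms 1 and 2 from a likelihood-based repeated-measures model of PROMIS-29 function at 3, 6 and 12 months, with arm, visit, arm-by-visit and baseline. Include every patient with a baseline and any follow-up score. Keep the completers' t test as a supporting analysis. Report deaths before 1 year by arm, with a sensitivity analysis for them, such as assigning a poor score.
3. **Allowance.** State it as 36 per arm to give 30 evaluable at 1 year (16.7% loss), without the 5-year reference.

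**Cost.** Changes of wording and slightly more analysis work. No new visits, data or patients are needed, and the sample size stays the same. The model relies on a missing-at-random assumption, which should be stated; it reduces but does not remove bias if missingness depends on the unobserved 1-year score.

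### The secondary aim asks whether CIRT improves local control over PT, but the test assigned to it is a noninferiority test, which can be positive with no advantage for CIRT

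*Protocol article*

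**What the plan says.** Section 2 (Research Methods and Analysis) words the aim as superiority: "The secondary aim of the study is to determine whether CIRT improves local control in comparison with PT". The reason given there is that CIRT is thought to be biologically more effective than lower-LET radiotherapy "for treating radioresistant tumors and may reduce the risk of local recurrence".

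Section 2.6 (Statistical Consideration) repeats the directional wording, "Analyses for the secondary aim of determining whether CIRT improves local control in comparison with PT", and sets the analysis for when the last treated patient has 3 years of follow-up. The endpoint is "The proportion of patients with local control at 3 years and 95% CI", and the same sentence attaches the test to it: "in treatment arms 1 and 3 will be calculated with a one-sided noninferiority test". Arm 1 is CIRT and arm 3 is PT.

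Section 2.6 then lists Kaplan-Meier with likelihood ratio tests for all clinical outcomes, local recurrence among them, with analyses by histology. It does not connect these to the secondary aim.

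**The concern.** The aim and the test address different hypotheses. The aim needs evidence that the difference in local control (CIRT minus PT) is above zero. A noninferiority test gives evidence that the difference is above some negative number. The second can hold when the first does not, including when CIRT is somewhat worse. The rationale in Section 2 points to a gain, and nothing in the article explains why noninferiority would be the question.

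At stake is what may be claimed. A positive noninferiority result, reported under an aim worded as improvement, could be read as showing that CIRT controls tumours better than PT. The article says its benchmark figures may be used to design later Phase III trials, so a misread result could carry forward. The mismatch does not depend on any document not shown: whatever margin is used elsewhere, the test named here does not test the aim stated here.

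**Working it through.** **1. The article's own sample size.** Inputs from Section 2.6: mean decreases of 2 and 4.6 points, SD 4, one-sided α = 0.05, 80% power.

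- Normal approximation: n = 2 × (1.645 + 0.842)² × 4² / 2.6² = 29.3, so 30 per arm.
- Exact one-sided t test with 30 per arm: power 80.0%.

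The figure reproduces. It was derived for PROMIS-29 function only; no rate, alpha or power is stated for local control.

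**2. Can the named test be positive without any advantage?** Take 30 evaluable patients per arm and 22 controlled in each (an illustrative result).

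- p = 22/30 = 0.733 in both arms; difference 0.
- SE = √(2 × 0.733 × 0.267 / 30) = 0.114.
- One-sided 95% lower bound = 0 - 1.645 × 0.114 = -0.188, or -18.8 points.
- Two-sided 95% CI = ±1.96 × 0.114 = ±22.4 points.

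An assumed 20-point margin is met, although the observed advantage is nil and the two-sided interval is centred on zero. The article gives no margin, so 20 points is an assumption.

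The result depends on that margin. With true control of 75% in both arms, SE = √(2 × 0.75 × 0.25 / 30) = 0.112, and the chance of a positive test at one-sided 5% is Φ(margin/SE - 1.645):

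| Assumed margin (points) | Chance of a positive test, no true difference |
|---|---|
| 5 | 11.6% |
| 10 | 22.6% |
| 15 | 38.1% |
| 20 | 55.7% |

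Every positive result in this table would occur with no true improvement.

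**3. What a test matching the aim would deliver with 30 per arm.** Half-width of a two-sided 95% CI for the difference, with equal assumed rates p in the two arms = 1.96 × √(2p(1 - p)/30):

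| Assumed control, both arms | SE | Half-width (points) |
|---|---|---|
| 70% | 0.118 | 23.2 |
| 75% | 0.112 | 21.9 |
| 80% | 0.103 | 20.2 |
| 85% | 0.092 | 18.1 |

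Power to place that interval wholly above zero is Φ(difference/SE - 1.96), with unpooled SE:

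- 75% vs 85%: SE = √((0.75 × 0.25 + 0.85 × 0.15)/30) = 0.1025; Φ(0.10/0.1025 - 1.96) = 16%.
- 75% vs 90%: SE = √((0.75 × 0.25 + 0.90 × 0.10)/30) = 0.0962; Φ(0.15/0.0962 - 1.96) = 34%.

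With pooled variance under the null the values are 15.9% and 33.0%. At one-sided 5% they would be about 25% and 45 to 47%, but a two-sided 95% interval corresponds to one-sided 2.5%, so the lower figures apply.

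**4. Source of the rates.** The Introduction's 70% to 75% for definitive radiotherapy is set against a 5-year surgical figure for sacrococcygeal chordoma. The endpoint here is 3-year control across six histology groups. All local control rates above are therefore assumptions.

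**The case against.** The strongest reply is that the plan holds more than the noninferiority test. Section 2.6 also reports the 3-year proportions with 95% CIs and applies likelihood ratio tests to local recurrence. A reader might infer from the mismatch that the trial can say nothing on superiority. That goes too far: either analysis could reveal a difference. What remains is that neither is assigned to the secondary aim. No decision rule links a CI for the difference to a claim of improvement, and no step from noninferiority to superiority is described.

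A reader might also count the absent margin as an error. A condensed article may leave a margin to the full protocol or SAP, so its absence here is no finding, and supplying one would not turn noninferiority into improvement.

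Nor is the low power for local control a separate fault. The article claims power only for the primary comparison, and a secondary endpoint need not drive the sample size.

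It can fairly be added that this is a secondary aim in a nonrandomized cohort study that presents its results as benchmarks and admits potential bias. That lowers the severity but does not remove the conflict: this is the article's one named secondary aim, with its own timed analysis.

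**Conclusion.** The point holds as a conflict between the stated aim and its assigned test. The aim is worded as improvement in two places and has a superiority rationale; the test assigned to it can succeed with no advantage for CIRT. The 22/30 example, with its lower bound of -18.8 points, shows this under an assumed 20-point margin. The logic holds for any positive margin; only the frequency of such results changes with it.

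The conflict should be fixed, though it is not critical. The primary comparison and its 30 per arm are unaffected. The precision and power figures rest on 30 evaluable patients per arm, normal approximations and assumed control rates, and serve only to show what a matching analysis can be expected to deliver.

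**What to change.** Align the test with the aim. Given the rationale in Section 2, the direct repair is to replace the noninferiority sentence in Section 2.6 with:

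> The difference in 3-year local control (arm 1 minus arm 3) will be estimated with a two-sided 95% CI; CIRT is concluded to improve local control only if the interval lies wholly above zero.

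Two other repairs would be coherent: a prespecified sequence of noninferiority followed by superiority, or rewording the aim in both sections as noninferiority with a justified margin. The sponsor should choose one before the data are analysed.

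Whichever is chosen, add that a noninferiority result will not be reported as improvement. With the replacement sentence, also state the expected precision with 30 per arm and the low power for plausible gains, with the assumed rates shown. If the likelihood ratio test on local recurrence is meant to serve this aim, say so and give its role.

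The cost is a few sentences of wording. It needs no extra patients, visits or data.
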